### Data processing and analysis plan

Data will be statistically analyzed using IBM Statistics SPSS for Windows 23.0. The primary outcome will analyze all randomized patients (on an intent-to-treat (ITT) basis) and per-protocol (PP) population. The mean pain scores at rest and their standard deviations will be computed and compared using one-way ANOVA tests. VAS will be stratified as ordinal (0 as no pain, 1–3 as mild, 4–6 as moderate, and 7–10 as severe); the significance of the difference in the mean scores between local and saddle groups will be determined by the Kruskall-Wallis (*H*) test at 95% confidence interval, regarding *p* < 0.05 as statistically significant; furthermore, the mean pain scores will be analyzed for significant differences in the area under the curve (AUC) for VAS (2-sample *t*-test). The mean operative time and standard deviation will be computed for each technique of open hemorrhoidectomy. Cross tabulation will be performed between the two open hemorrhoidectomy techniques for categorical cost-effective analysis. The difference in the means will be compared using the *t*-test and their corresponding two-tailed p-value, regarding *p* < 0.05 as statistically significant.

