### Sample size determination

The randomized control trial assumes a null hypothesis that the mean postoperative pain scores after hemorrhoidectomy using local anesthesia are not different from that done under saddle block by a clinically relevant amount. Since the primary outcome measure was a continuous variable (i.e., pain level measured using a visual analog scale), the formula for an equivalence design in randomized control trials by Zhong et al. [15] was used.$$\boldsymbol{N}=\mathbf{2}\times {\left\{\frac{{\boldsymbol{Z}}_{\mathbf{1}-\propto}+{\boldsymbol{Z}}_{\mathbf{1}-\boldsymbol{\beta}}}{\boldsymbol{\delta}}\right\}}^{\mathbf{2}}\times {\boldsymbol{S}}^{\mathbf{2}}$$

where

***N***sample size per group

***Z***_***1−α***_standard normal deviate for a two-sided test used in equivalence trials (1.96 for 95% confidence interval)

***δ***clinically admissible margin of equivalence design as a difference

***α***type I error associated with rejecting the null hypothesis when it is true; (0.05) for 95% confidence interval

***β***type II error associated with the alternative hypothesis, assumed to be 0.20 for a statistical power of 80%

**(1−*****β*****)**the probability of rejecting the null hypothesis when it is false, i.e., *Z*_1−*β*_ = 0.845 for statistical power of 80%

***S***^**2**^pooled standard deviation of both comparison groups

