### Study variables

#### Primary outcome variable

The occurrence of pain following open hemorrhoidectomy will be determined in both groups using the area under the curve (AUC) for visual analog scale (VAS). The VAS will be used in an interval of 2, 4, and 6 h and 7 days postoperatively (the lower end of the scale labeled “0” means no pain while the upper end of the scale “10” signifies the worst imaginable pain).

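### Pain, declared as a VAS AUC, is tested three ways with none named as decisive, and two of the tests have no stated unit or time point

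*Protocol article*

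**What the plan says.** The protocol's Primary outcome variable section says that pain "will be determined in both groups using the area under the curve (AUC) for visual analog scale (VAS"). The same section sets four readings per patient: "The VAS will be used in an interval of 2, 4, and 6 h and 7 days postoperatively".

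The Data processing and analysis plan section then names three comparisons of that outcome:

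- For the scores: "The mean pain scores at rest and their standard deviations will be computed and compared using one-way ANOVA tests".
- For the VAS cut into four grades: "the significance of the difference in the mean scores between local and saddle groups will be determined by the Kruskall-Wallis (*H*) test". The p < 0.05 rule is attached to this test.
- As a further analysis: "the mean pain scores will be analyzed for significant differences in the area under the curve (AUC) for VAS (2-sample *t*-test").

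The section closes with a t-test of means and "their corresponding two-tailed p-value, regarding *p* < 0.05 as statistically significant". I take 0.05 as the level for all three pain tests, since no other is given. The section does not rank them. For ANOVA and Kruskal-Wallis it names neither a time point nor whether the analysed value is one reading, a patient's mean or all readings together.

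**The concern.** Each patient contributes four correlated readings. One-way ANOVA and Kruskal-Wallis have no term for patient or time, so their error rate depends on what is fed to them, and the section leaves that open. The AUC reduces each patient to one value and avoids the difficulty, but it comes last and is not identified as the deciding test.

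The consequence is a main pain result that is not fixed in advance. The three tests can disagree, and the text does not say which then stands. If a significant result on any of them may be reported as the finding, the 5% level no longer describes the risk of a false one.

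**Working it through.** **Inputs from the protocol.** 29 patients per arm; readings at 2, 4, 6 h and day 7; S = 1.9 (Sample size determination); level 0.05, two-tailed. The plan gives no other error rate to reproduce.

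**Assumptions, because the protocol gives no figures.** Within-patient correlation ρ is equal for all pairs of readings, with range 0.2–0.8. Three patterns of time means were used: level; 2, 4, 4, 2; and 4, 5, 5, 1 (4 and 6 h one point above 2 h, day 7 three points below it). Trials were simulated with no true difference between arms.

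**1. AUC t-test alone.** One value per patient. The simulated false-positive rate is 4–5.5%, the nominal level apart from simulation error.

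**2. All three tests on one value per patient.** Here ANOVA uses the patient's mean, Kruskal-Wallis uses the grade of that mean, and the t-test uses the AUC. If the tests were independent, the chance of at least one p < 0.05 would be 1 − 0.95³ = 14.3%. They are correlated, and simulation gives about 8–10%.

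**3. ANOVA and Kruskal-Wallis at each time, plus AUC.** A single-time ANOVA holds its level (4–6%). Over four times, the independent case is 1 − 0.95⁴ = 18.5%. Simulated rates for at least one p < 0.05 are 13–18% for the four ANOVAs and 15–19% for the four Kruskal-Wallis tests (ρ 0.25–0.7). With all nine tests and means 2, 4, 4, 2, the rate is 26% at ρ = 0.2, 22% at 0.5 and 17% at 0.8. Over the time patterns considered, the range is about 16–26%. This is multiplicity; no single test in it lacks a term that it needs.

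**4. All four readings pooled as independent (not stated in the text).** 58 × 4 = 232 observations. The true variance of the arm difference exceeds the assumed variance by

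D = (1 + 3ρ) × σ² / (σ² + τ²),

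where σ² = 1.9² = 3.61 and τ² is the variance of the time means, which a one-way ANOVA leaves in its residual. The false-positive rate is P(|Z| > 1.96/√D).

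| Time means | τ² | ρ | D | Rate |
|---|---|---|---|---|
| level | 0 | 0.2 | 1.60 | 12.1% |
| level | 0 | 0.5 | 2.50 | 21.5% |
| level | 0 | 0.8 | 3.40 | 28.8% |
| 4, 5, 5, 1 | 2.69 | 0.2 | 1.6 × 3.61/6.30 = 0.92 | 4.1% |
| 4, 5, 5, 1 | 2.69 | 0.5 | 2.5 × 3.61/6.30 = 1.43 | 10.2% |

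Simulation at ρ = 0.5 agrees: 20.3% with level means and 10.0% with the trend. The pooled rate therefore runs from about 4% to about 30%, depending on two quantities that the protocol does not give.

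**The case against.** The strongest reply is that the outcome section already declares the AUC, its t-test is valid, and the order of sentences in the analysis section does not override that declaration. This stands for the AUC test itself: the repeated readings are properly handled there. It does not settle the role of the other two tests, which are applied to the same outcome, one of them with its own explicit significance rule.

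A second reply is that nothing in the text says readings are pooled, and that the sample size formula uses one score per patient, which fits a per-patient analysis better. This also stands. Pooling is one possible reading and cannot be presented as the plan.

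A third is that tests run separately at each time each hold 5%. That is correct; the excess in that case comes from counting several tests.

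A fourth is that an article leaves unit and time point to a fuller plan. In part it does, and the lack of model detail alone would not be a finding. But the article itself names three tests for one outcome and gives none of them precedence.

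Finally, replacing everything with an equally weighted average of the four readings would displace the declared AUC with a different quantity. This is a fair objection to such a remedy, and the change proposed below keeps the AUC.

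**Conclusion.** The point holds as a matter of unranked tests and unstated units. The AUC t-test keeps about 5%. If any stated test may count, the risk of at least one false p < 0.05 is about 8–10% on the most favourable reading and about 16–26% with testing at each time, for assumed correlations of 0.2–0.8.

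A reader might infer two stronger conclusions that the documents do not support:

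- **That ignoring within-patient correlation puts the plan's error rate at about 14–22%.** Pooled ANOVA and Kruskal-Wallis rates in that range need pooling, which is not stated, and particular choices of correlation and time trend. Rates of that size from separate tests at each time have a different cause, multiplicity.
- **That a too-narrow pooled interval would falsely declare equivalence against 0.73.** The analysis section plans no interval set against that value, so the error rate of such an interval is not a property of this plan.

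**What to change.** In the Data processing and analysis plan section:

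1. Name the between-arm difference in AUC, one value per patient, with its confidence interval, as the single decisive pain comparison, in line with the outcome section.
2. Replace the one-way ANOVA and Kruskal-Wallis significance tests with one supportive linear mixed model: arm, time, arm-by-time and a within-patient covariance. Report the differences at 2, 4, 6 h and day 7 with intervals.
3. Report the pain grades as a descriptive table.
4. State that the four readings are not pooled as independent observations.

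The supportive model is worth having. If the AUC is a trapezoid in hours (an assumption, since the article gives no rule), the stretch from 6 h to day 7 is 162 of 166 h, and the 2 h and 4 h readings carry weights of only 1/166 = 0.6% and 2/166 = 1.2%. Early pain would then be visible mainly in the time-specific estimates.

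The cost is wording only, with no new patients or data, but fewer p-values can be claimed. The interim analysis, planned to evaluate the primary outcome, was done on 10 March 2022, and 45 of 58 patients were registered by 7 April 2022. The amendment must therefore be dated and described as made after that look, with the reason given.

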According to a similar randomized control trial that compared open hemorrhoidectomy under local anesthesia versus supine anesthesia at the Korle Bu Teaching Hospital in Ghana [16], the difference in the mean pain scores between the 2 groups was *δ* = 0.73; pooled standard deviation in the mean pain scores *S* = 1.9 (average of 2.356 for local anesthesia and 1.479 for supine anesthesia), an estimated sample size of 104 participants per group, was obtained. Since at the time of the proposed study, nothing was known about the mean pain score following OH under local anesthesia and the real difference in clinical outcome between the two techniques in Uganda, the sample size was adjusted using Slovin’s formula as detailed by Ellen [17] based on the hospital records, Kampala International University Teaching Hospital which registered an average of 33 cases of grade 3 or 4 hemorrhoids in a period of 6 months that corresponded to the intended data collection period; thus, a sample size of 26 participants per group was obtained which was increased to 29 participants in each arm, based on a rate of 10% in each arm to compensate for the loss to follow-up and non-responsiveness found.

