### Trial discontinuation

The trial will be discontinued for individual patients due to non-adherence, e.g., not completing the specified duration of follow-up, diverse outcomes, e.g., too much pain resulting in converting from local to GA (cross over) and getting other analgesics other than those prescribed in the trial.

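### One-way ANOVA pools variances that the plan's own SDs suggest are unequal; this is harmless at 29:29, but the error rate is off in either direction once the analysed arms differ in size

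*Protocol article*

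**What the plan says.** All places are in the protocol article.

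- **Data processing and analysis plan.** For resting pain: "The mean pain scores at rest and their standard deviations will be computed and compared using one-way ANOVA tests". A Kruskal-Wallis test on the categorised VAS follows. Then "the mean pain scores will be analyzed for significant differences in the area under the curve (AUC) for VAS", by a 2-sample t-test whose variance form is not given. The primary outcome is to be analysed in both the intention-to-treat (ITT) and the per-protocol set.
- **Primary outcome variable.** Pain "will be determined in both groups using the area under the curve (AUC) for visual analog scale (VAS", so the AUC is the primary variable. The ANOVA is attached to the mean scores.
- **Sample size determination.** The SD of 1.9 is described as the "average of 2.356 for local anesthesia and 1.479 for supine anesthesia", taken from an earlier trial. The plan is 29 per arm, after a 10% loss allowance applied equally to both arms. Type I error is 0.05, with a normal deviate of 1.96 described as two-sided.
- **Randomization and blinding.** Half of the envelopes go to each arm.
- **Trial discontinuation.** Individual patients may be discontinued, for example for "too much pain resulting in converting from local to GA (cross over"). Ancillary and post-trial care also describes conversion from local anesthesia only, but to SA. The two sections need to be reconciled, though the point here does not depend on which is meant.
- **Interim analysis** and **Unblinding.** Withdrawal for a failed anesthetic technique is not limited to one arm.

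**The concern.** A one-way ANOVA with two groups estimates one common variance. If the true variances differ, the pooled standard error is still right when the arms are equal in size, but not otherwise. If the more variable arm is the smaller, the pooled standard error is too small, intervals are too narrow and the test rejects too often. If the more variable arm is the larger, the reverse holds.

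The plan's own SDs make unequal variances the natural working assumption, and the document contains several routes to unequal arms: conversion from local anesthesia, withdrawal for failed technique, incomplete follow-up, and a planned per-protocol analysis. At stake is whether the reported p-values and intervals for mean pain carry their nominal 5% and 95% in those sets.

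**Working it through.** **Inputs from the protocol article.** SD 2.356 (local) and 1.479 (comparator), difference 0.73, two-sided alpha 0.05 with z = 1.96, z = 0.845 for 80% power, 29 per arm (26 before the loss allowance). **Assumptions.** Normal scores, and the size of any loss from either arm.

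**Step 1: the plan's own figure.** The mean of the two SDs is (2.356 + 1.479)/2 = 1.9175, which the plan gives as 1.9. Its formula then yields 2 × ((1.96 + 0.845)/0.73)² × 1.9² = 106.6, against the stated 104. That is close enough to confirm that these SDs are the planning basis. Also 26/0.9 = 28.9, which gives the stated 29.

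**Step 2: the variance ratio.** 2.356/1.479 = 1.593, and 1.593² = 2.54.

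**Step 3: standard errors.** With n₁ local and n₂ saddle patients:

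- true SE = √(2.356²/n₁ + 1.479²/n₂)
- pooled SE = √{[(n₁ − 1)2.356² + (n₂ − 1)1.479²]/(n₁ + n₂ − 2) × (1/n₁ + 1/n₂)}

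At 29:29 both equal 0.517.

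At 26:29 the true SE is √(5.551/26 + 2.187/29) = 0.538. The pooled SE is √[(25 × 5.551 + 28 × 2.187)/53 × (1/26 + 1/29)] = 0.525, which is 2.4% too small.

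At 29:20 the true SE is 0.548 and the pooled SE 0.595, which is 8.5% too large.

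**Step 4: error rates.** Simulation with equal means, 400,000 trials per row, nominal two-sided 5%:

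| Local : saddle | Pooled SE / true SE | Pooled (ANOVA) error | Welch error |
|---|---|---|---|
| 29:29 | 1.000 | 5.0% | 4.9% |
| 26:29 | 0.976 | 5.7% | 5.0% |
| 23:29 | 0.950 | 6.3% | 5.0% |
| 20:29 | 0.921 | 7.2% | 5.0% |
| 29:26 | 1.024 | 4.6% | 5.0% |
| 29:23 | 1.052 | 4.1% | 5.1% |
| 29:20 | 1.085 | 3.5% | 5.0% |

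Repeat runs moved the pooled entries by about 0.1 to 0.2 percentage points (5.6% to 5.7% at 26:29, 7.0% to 7.2% at 20:29). Coverage of the pooled 95% interval is 94.3% at 26:29, 93.7% at 23:29 and 92.8% at 20:29.

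**Step 5: the price of Welch when it is not needed.** At 29:29 the 95% half-width is 1.035 pooled and 1.039 Welch, an increase of 0.4%.

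**The case against.** The strongest reply is that the plan as designed shows no distortion. Allocation is 1:1, the loss allowance is the same in both arms, and an ITT analysis keeps converted patients in their arm. **This stands for complete 29:29 data.** It does not cover the per-protocol set. It covers the ITT set only if outcomes are collected after conversion or withdrawal, and the missing-data section says only that missing values will be reported as missing.

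A reader might infer that unequal arms as such make the results too optimistic, or that the local arm must end up smaller because only its conversion is described. **The documents support neither.** With a smaller saddle arm the pooled test is conservative. Withdrawal for failed technique applies to either arm, failed technique is a general exclusion criterion, and the introduction lists failed block among the problems of saddle block. No conversion rate is given. An error near 7% needs 9 of 29 local patients (31%) lost and none from the other arm, about three times the planned allowance.

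The variance form of the AUC t-test is open and may be settled in a separate analysis plan. The planning SDs are for an external trial's mean pain scores, not for the AUC. **Both points stand:** the ratio of 2.54 is not established for the primary variable, and only the ANOVA fixes a pooled method.

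The simulation removes patients at random, whereas the described reason is too much pain. In the limiting case where the highest scorers leave the local arm, its SD falls to about 1.99 (n = 26), 1.79 (23) and 1.64 (20), and its mean shifts by −0.45 to −1.17. Rejection rates are then nearly the same for pooled and Welch: 18% against 17%, 43% against 41%, 69% against 67%. **This stands.** Selection bias would dominate, and Welch does not repair it.

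A reader might also infer that pooling could produce a false equivalence claim. It would not at this size. If a 95% interval were held against ±0.73, both half-widths exceed 1.0, and at a true difference of 0.73 simulated false equivalence is at most 0.005% with either method. Under the difference tests actually written, a standard error that is too small makes a finding of no difference harder to reach.

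**Conclusion.** The concern holds as a minor robustness point. The protocol fixes a pooled-variance comparison of mean pain while its own planning SDs speak against equal variances. The effect is nil at 29:29. With a smaller local arm the two-sided error is about 5.6% at 26:29 and 7% at 20:29. With a smaller saddle arm it is about 4.6% at 29:26 and 3.5% at 29:20. Welch stays at about 5% throughout.

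These figures rest on normal scores, on the external SDs applying here, and on assumed losses unrelated to pain. They do not show that the trial's results will be too optimistic, that any equivalence conclusion would change, or that the primary AUC test is wrong. What remains is that pooled error bars are not correct when arms differ in both size and variance, and that the remedy is essentially free.

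**What to change.** In the data processing and analysis plan:

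1. Replace the one-way ANOVA for mean pain scores by Welch's two-sample t-test.
2. State that the 2-sample t-test on the AUC uses the unequal-variance form.
3. Build the confidence interval for each mean difference from the Welch standard error and its degrees of freedom, in both the ITT and the per-protocol set.

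**Cost:** a phrase or two of text. SPSS already prints the unequal-variance line for a two-sample t-test. The interval at 29:29 widens by 0.4%. Naming the form in advance also removes a choice between two printed results once the data are seen.

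This change does not address bias from leaving converted patients out of the per-protocol set, which has to be considered separately when that set is interpreted.

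### Minor: Kruskal-Wallis on four VAS grades cannot show the difference in mean scores it is said to test and loses some power; the grade limits also leave gaps on a continuous scale

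*Protocol article*

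**What the plan says.** Under Sample size determination, the Protocol article treats pain as continuous: "Since the primary outcome measure was a continuous variable (i.e., pain level measured using a visual analog scale"). Under Primary outcome variable it gives the ends of the scale ("the lower end of the scale labeled “0” means no pain while the upper end of the scale “10” signifies the worst imaginable pain") and says that pain "will be determined in both groups using the area under the curve (AUC) for visual analog scale (VAS"). Neither section states a recording precision or a rounding rule.

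The section Data processing and analysis plan then lists three comparisons of pain between the arms:

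- An ANOVA on the scores: "The mean pain scores at rest and their standard deviations will be computed and compared using one-way ANOVA tests".
- A grading of the VAS, "VAS will be stratified as ordinal (0 as no pain, 1–3 as mild, 4–6 as moderate, and 7–10 as severe"), followed in the same sentence by "the significance of the difference in the mean scores between local and saddle groups will be determined by the Kruskall-Wallis (*H*) test", with p < 0.05 as the criterion.
- A two-sample t-test on the AUC: "the mean pain scores will be analyzed for significant differences in the area under the curve (AUC) for VAS").

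The section does not rank the three.

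**The concern.** There are two faults in the grading sentence.

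**Variable and claim do not match.** The sentence turns the VAS into an ordinal variable and then names a rank test. The ungrouped scores already have the ANOVA and the AUC has the t-test, so the only evident use of the grades is as input to Kruskal-Wallis. Yet the test is said to judge mean scores. Kruskal-Wallis compares ranks, not means. On four grades it treats 1 and 3 as the same and 3 and 4 as a full step apart. Information is discarded before testing, in a trial with 29 per arm against the 104 that its own calculation called for.

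**The limits are not contiguous.** On a continuous scale, a reading of 0.4, 3.5 or 6.6 belongs to no grade. If the recode is programmed literally, such readings become missing in the Kruskal-Wallis test and in any severity table.

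At stake are the sensitivity and meaning of one of the three pain p-values, and the completeness of the severity table.

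**Working it through.** **Plan's own figures.** The article gives no power for the Kruskal-Wallis test and no share of ungraded readings, so there is nothing to reproduce on this point. As a check that the planning inputs are read correctly, the sample-size formula gives 2 × ((1.96 + 0.845)/0.73)² × 1.9² = 106.6, close to the stated 104 per group. That result has no bearing on the grading.

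**Inputs from the Protocol article (Sample size determination).** SDs 1.479 and 2.356, working SD 1.9; difference 0.73; two-sided α = 0.05; 29 per arm.

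**Assumptions, because the article gives no values.** Shape of the VAS distribution (normal, clipped to 0–10), control-arm mean, recording precision, and a second true difference of 2 × 0.73 = 1.46.

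**Step 1: can four grades show a mean difference?** Suppose every patient in one arm scores 1 and every patient in the other scores 3. The means differ by 2 points, 2/0.73 = 2.7 times the planning difference, but all patients are graded mild and the graded data are identical. If the scores are 3 and 4, the means differ by 1 and the grades separate completely. A test on grades is therefore not a test of mean scores.

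**Step 2: power lost by grading.** Simulated Kruskal-Wallis power, 29 per arm, SD 1.9 in both arms, control means between 2 and 4:

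| Input to the test | Difference 1.46 | Difference 0.73 |
|---|---|---|
| Ungrouped VAS | about 80% | 28–30% |
| Ungrouped VAS in whole numbers | 78–80% | about 28% |
| Grades without gaps | 71–74% | 24–25% |
| Grades exactly as written, gaps set to missing (0.1-point readings) | 61–64% | 20–21% |

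At 1.46, gap-free grades cost about 6–8 percentage points. At 0.73 they cost about 3–6. Rounding to whole numbers and then grading gives 72–74% at 1.46, so the loss comes from the grouping and not from the recording precision.

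A second simulation used unequal SDs (1.479 and 2.356), control means 2 to 5, and rounding before grading. At a difference of 1.5, power was 79% on the ungrouped VAS and 71–76% on grades, a loss of about 4–8 points. At 0.73 it was 27–28% and 24–26%, a loss of about 2–3 points.

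**Step 3: share of readings without a grade.** The gaps (0,1), (3,4) and (6,7) cover 3 of 10 scale units.

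- Whole-number readings: 0%.
- Half points: 3 of 21 possible values, 3/21 = 14.3% if all are equally likely; 14–17% under clipped normals with means 1–6 and the article's SDs.
- Readings to 0.1: 27 of 101 possible values, 27/101 = 26.7% if equally likely; 25–30% under the same clipped normals. At the top of that range, 0.30 × 58 = 17 readings per time point.
- Continuous readings under truncated rather than clipped normals, location 1–7: 25–42%. The share is higher at low pain because truncation spreads into (0,1) the mass that clipping places at exactly 0, which does have a grade.

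**Step 4: which analyses use the grades?** The ANOVA is on mean scores and the t-test on the AUC. Every reading, graded or not, enters both.

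**The case against.** The strongest reply is that the pain comparison does not depend on the grades. The primary outcome variable is the AUC, it has its own t-test, and the ANOVA also uses ungrouped scores. This stands in full. A reader might infer that the grading hides real pain differences or discards primary-outcome readings; the article does not support that.

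Second, the sentence says mean scores, so the test may be meant for the scores, in which case nothing is lost. The wording is ambiguous, but grading is the less strained reading, since the grades have no other stated use. Either way the sentence needs correcting: it should name the variable, and the test is not one of means.

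Third, limits such as 1–3 and 4–6 fit whole-number scores, and the day-7 assessment may be done by telephone, where a patient cannot mark a line. Calling the outcome continuous justifies a sample-size formula; it does not fix the recording precision. This also stands. A reader might infer that about 30% of readings are lost, but that needs 0.1-point recording and a recode to missing, neither of which is documented. Nor is 30% a ceiling, as the truncated normals show. The 61–64% power rests on the same two assumptions.

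Fourth, the loss of sensitivity might be read as tilting an equivalence trial towards its hypothesis. That objection is to using difference tests for equivalence at all, and correcting the grades would not answer it. Finally, no treatment decision in the article uses the grades; the gap from 3 to 4 lies below its analgesia threshold of more than 4.

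Recode details can be left to a fuller document. Here, however, the article states explicit limits that do not fit the scale it describes, and that is open to comment.

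**Conclusion.** The point holds in a limited form and is minor. On the natural reading, Kruskal-Wallis is run on four grades and described as a test of mean scores, which it cannot be. The cost to that one test is about 6–8 percentage points of power at an assumed difference of 1.46 (about 80% to 71–74%) and about 3–6 points at 0.73, where power is below 30% in any case. These figures assume normal VAS values clipped to 0–10, SD 1.9, control means of 2–4 and 29 analysed per arm; the loss persists with whole-number readings.

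Separately, the limits do not cover a continuous scale. The affected share runs from 0% (whole numbers) through about 14–17% (half points) to 25–30% (0.1 points, clipped normals), and the article does not say which precision applies. The consequence is confined to the Kruskal-Wallis result and the severity table. The AUC t-test and the ANOVA are untouched.

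**What to change.** In Data processing and analysis plan, separate the grading from the test:

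- Run Kruskal-Wallis on the ungrouped VAS reading at each time point, describe it as a comparison of distributions and not of means, and state that it supports the AUC analysis.
- Keep the four grades for descriptive tables only. Either state that the VAS is recorded in whole numbers, or make the limits contiguous, for example 0, above 0 to 3, above 3 to 6, and above 6 to 10.

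The cost is about one sentence and a changed recode, with no new data or patients. The one downside is that the p-value no longer refers to the none/mild/moderate/severe table, which becomes purely descriptive.

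### The Kruskal-Wallis test on four pain grades is assigned to the difference in mean VAS, but it compares grade distributions, so a significant result is not evidence of a difference in means

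*Protocol article*

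**What the plan says.** *Sample size determination* frames the trial's hypothesis in terms of means: whether the "mean postoperative pain scores after hemorrhoidectomy using local anesthesia are not different from that done under saddle block by a clinically relevant amount". It plans on a pooled SD of 1.9, explained as the "average of 2.356 for local anesthesia and 1.479 for supine anesthesia", both taken from one cited trial in Ghana.

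*Data processing and analysis plan* lists three analyses of pain:

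- Mean pain scores at rest are compared by one-way ANOVA.
- The scale is then cut up: "VAS will be stratified as ordinal (0 as no pain, 1–3 as mild, 4–6 as moderate, and 7–10 as severe"). In the same sentence, "the significance of the difference in the mean scores between local and saddle groups will be determined by the Kruskall-Wallis" test, "regarding *p* < 0.05 as statistically significant".
- The AUC for VAS is compared by a two-sample t-test.

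*Primary outcome variable* makes the AUC the primary measure. No mean VAS for either arm appears anywhere in the article, and *Sample size determination* says that the mean pain score under local anesthesia was unknown in Uganda.

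**The concern.** The sentence joins a statement about means to a test that is not about means. Kruskal-Wallis on four ordered grades uses only the ranks of the grades, and its reference distribution assumes the same grade distribution in both arms. It can be read as a test of location only if the two distributions share shape and spread. The only spreads the protocol offers are clearly unequal, on a scale that stops at 0. Near that floor, equal means do not give equal grade distributions.

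Two things are at stake. A p-value below 0.05 from this test could be reported as a difference in mean pain when the means are the same. Grading also discards information, so a real difference in means may be detected less often than on the full scale.

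**Working it through.** **Inputs.** Grade cut-points: "0 as no pain, 1–3 as mild, 4–6 as moderate, and 7–10 as severe". Two-sided 0.05 level. SDs 2.356 (local) and 1.479 (comparator). 29 patients per arm. Common mean VAS: not in the document, so assumed over a range.

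**The plan's own figure.** With "1.96 for 95% confidence interval" and 0.845 for 80% power, the stated formula gives N = 2 × ((1.96 + 0.845)/0.73)² × 1.9² = 2 × 14.76 × 3.61 = 106.6, so 107 per group. The article states 104, a difference of under 3%. Averaging the two SDs gives (2.356 + 1.479)/2 = 1.9175, stated as 1.9. The final size also follows: 26/0.9 = 28.9, so 29. The SDs and n used below are therefore the plan's own.

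**Why equal means need not give equal grades.** Take a rounded beta distribution on 0–10 with mean 1.5 in both arms and exactly the two cited SDs. The proportions in the four grades are:

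- local: 0.554, 0.276, 0.105, 0.065
- comparator: 0.287, 0.606, 0.100, 0.006

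P(local grade lower) = 0.554 × 0.712 + 0.276 × 0.106 + 0.105 × 0.006 = 0.424. P(local grade higher) = 0.276 × 0.287 + 0.105 × 0.893 + 0.065 × 0.993 = 0.238. The means are identical, yet a patient under local anesthesia ranks below a comparator patient far more often than above. The rank test responds to that imbalance.

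**Rejection rate with equal means.** Integer VAS with SDs matched exactly, 29 per arm, 40,000 simulated trials per cell, tie-corrected Kruskal-Wallis on the grades, and a pooled t-test (the same as a two-group ANOVA) on the raw score. Ranges cover the beta, censored-normal and gamma shapes; at mean 6 only the first two were run.

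| Common mean VAS | Kruskal-Wallis on grades | t-test on raw VAS |
|---|---|---|
| 1.0 | 28–35% | about 7% |
| 1.5 | 23–28% | about 6% |
| 2.0 | 15–17% | 5–6% |
| 2.5 | 8–9% | about 5% |
| 3.0 | 5–6% | about 5% |
| 4.0 | 5–6% | about 5% |
| 5.0 | 5–7% | about 5% |
| 6.0 | about 5% | about 5% |

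When both arms share one distribution, the graded test holds 5%. The inflation therefore comes from unequal spread near the floor, not from the test's own calibration.

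**Power for a true 1-point difference.** On the raw score with the cited SDs, the standard error is √((2.356² + 1.479²)/29) = √(7.738/29) = 0.517, and 1/0.517 = 1.94. Against a critical value of about 2.00 this gives power of about 47%. In the beta simulation the graded test has these powers, by the lower of the two means (local anesthesia worse / better):

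- lower mean 3: 40% / 45%
- lower mean 4: 39% / 44%
- lower mean 5: 42% / 41%

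With equal SDs of 1.9 the raw-score standard error is 1.9 × √(2/29) = 0.499, giving power of about 50%, and the graded test reaches about 42–43%. Across these cases grading costs about 3–8 points. The split by direction depends on shape: under a censored normal the loss is larger when local anesthesia is worse, and can vanish when it is better at the low end of this range.

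**The case against.** The strongest reply is that the plan already contains the right analyses. The sentence before the quoted one compares mean scores by ANOVA, the clause after it applies a t-test to the AUC, and the AUC is the primary variable. A rank test applied just after the scale has been declared ordinal is a conventional pairing, and the clause may simply be loosely worded. This limits the damage: a false claim about mean pain would have to be made alongside two tests of means that hold close to 5%. It does not remove the error, because the text still assigns the significance of the mean difference to Kruskal-Wallis.

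A reader might infer that the cited SDs alone make the test reject at four to five times its nominal rate. They do not. That needs a low common mean, roughly 1.25 to 1.85, and the article gives no mean. At 2 the rate is about three times nominal, and from 3 to 6 there is little or no inflation. The one figure on pain level points away from low means: the *Introduction* reports severe pain in 20–40% of patients in earlier studies. In the beta model, mean 1.5 puts only about 7% and 1% of the two arms in the top grade, while mean 5 puts 29% and 16% there. The *Introduction* does not say when or how severity was measured, so this is weak evidence, but nothing in the article supports a mean of 1.5.

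A reader might also infer a general bias against detecting worse pain under local anesthesia. The strong asymmetry is confined to low means: with the lower mean at 1.5 the graded test has 28% power if local anesthesia is worse and 89% if it is better. In the beta model at lower means of 3 to 5 the two directions differ by at most about 5 points.

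**Conclusion.** The point stands as a mismatch between the stated question and the named test, and that part needs no simulation. Kruskal-Wallis on four grades tests equality of grade distributions, so a significant H does not show that mean VAS differs.

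The numerical consequence is conditional. With the cited SDs, 29 per arm and equal means, the false-positive rate for a claim about means runs from near nominal at mid-scale to about a quarter of trials at a mean of 1.5. These figures rest on SDs borrowed from a single cited trial, on assumed shapes, and on a mean that the protocol does not state. Away from the floor the cost is a modest loss of power, about 3–8 points for a 1-point difference under the beta shape. The documents do not support saying that the primary comparison itself is invalid, since that is the t-test on the AUC.

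**What to change.** In *Data processing and analysis plan*, delete the statement that Kruskal-Wallis determines the significance of the difference in mean scores. Base statements about mean pain on the ungraded VAS analyses already planned: the AUC t-test as primary, and the difference in mean VAS with a confidence interval. An unequal-variance (Welch) interval is preferable given the cited SDs, but optional, since with equal arms the pooled test also holds about 5%. Present the four grades as a descriptive table by arm. If Kruskal-Wallis is kept, label it a supportive comparison of grade distributions and draw no conclusion about means from it.

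The cost is a few lines of text, with no new data or patients. The one downside is that the clinical pain grades no longer carry a test presented as a test of means.
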